### Budget Impact Analysis

A municipal budget impact analysis is performed, subtracting possible savings for the municipality in relation to health care costs, nursing costs, and lost productivity from the investment costs [40]. As part of the budget impact analysis, the annual rate of return of municipality investments is estimated. Follow-up data covering 1 year before baseline until 3 years after are collected from national registers (Multimedia Appendix 2). To investigate the possible impact of the intervention on health care service usage by participants, pharmaceutical consumption and municipal service usage as annual consumption are compared to a reference year 1 year before the intervention (baseline minus 1 year).

As part of the analysis, the following two scenarios are examined: (1) A_0_, baseline scenario, where no intervention has been introduced. The health status of the examined population is expected to decrease, whereas the municipality costs are expected to increase; (2) A_1_, alternative scenario, where the eHealth lifestyle coaching intervention has been introduced. The health status of the examined population is expected to increase owing to the intervention, whereas municipal costs are expected to decrease.

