**Methods:**

We conduct a multicenter trial with a 1-year intervention and 1-year retention. LIVA 2.0 is implemented in municipalities within administrative regions in Denmark, specifically eight municipalities located within the Region of Southern Denmark and two municipalities located within the Capital Region of Denmark. The participants are assessed at baseline and at 6-, 12-, and 24-month follow-ups. Individual data from the LIVA 2.0 platform are combined with clinical measurements, questionnaires, and participants’ usage of municipality and health care services. The participants have a BMI ≥30 but ≤45 kg/m2, and 50% of the participants have type 2 diabetes. The participants are randomized in an approximately 60:40 manner, and based on sample size calculations on weight loss and intention-to-treat statistics, 200 participants are randomized to an intervention group and 140 are randomized to a control group. The control group is offered the conventional preventive program of the municipality, and it is compared to the intervention group, which follows the LIVA 2.0 in addition to the conventional preventive program.

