**Results:**

The first baseline assessments have been carried out in March 2018, and the 2-year follow-up will be carried out between March 2020 and April 2021. The hypothesis is that the trial results will demonstrate decreased body weight and that the number of patients who show normalization of their HbA_1c_ levels in the intervention group will be much higher than that in the control group. The participants in the intervention group are also expected to show a greater decrease in their use of glucose-lowering medication and a greater improvement in their QOL when compared with the control group. Operational costs are expected to be lower than standard care, and the intervention is expected to be cost-effective.

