### Health Economic Design

Within the scope of a cost-effectiveness analysis, expenditures related to the intervention, including acquisition, deployment, and operational costs, are compared with outcomes of the intervention in relation to the defined assessments. The cost effectiveness of the intervention is primarily assessed from the perspectives of the municipalities. The total cost of the intervention paid by a Danish municipality consists of investment costs as well as operating costs. Investment costs include expenditure for the training of health professionals as well as basic preparation cost. Operating costs cover the annual license fees for the individuals participating in the intervention as well as the individuals in the 1-year retention period. It is assumed that after 1 year in the intervention, participants will move to the retention period, where they will remain for 1 year; however, every year, 20% of the initial population will ultimately leave the intervention. Additionally, the operating costs include the salaries of the health professionals. The costs are compared to the effect of the intervention to evaluate cost effectiveness both in relation to the clinical effect and QOL [39].

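### As written, the budget impact analysis sets savings against investment costs alone, leaving out operating costs, and does not name the randomised control arm as its reference

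*Protocol article*

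**What the plan says.** Health Economic Design fixes the cost terms: "The total cost of the intervention paid by a Danish municipality consists of investment costs as well as operating costs". It then fills in each part:

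- Investment: "Investment costs include expenditure for the training of health professionals as well as basic preparation cost".
- Operating, licences: "Operating costs cover the annual license fees for the individuals participating in the intervention as well as the individuals in the 1-year retention period".
- Operating, staff: "Additionally, the operating costs include the salaries of the health professionals".

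The next section, Budget Impact Analysis, describes its calculation as "subtracting possible savings for the municipality in relation to health care costs, nursing costs, and lost productivity from the investment costs" and adds a yearly rate of return for the municipality. It does not mention operating costs.

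For service use the same section gives this reference: "pharmaceutical consumption and municipal service usage as annual consumption are compared to a reference year 1 year before the intervention (baseline minus 1 year". It then sets up two scenarios. In A0 no intervention is introduced and municipal costs are expected to rise. In A1 the eHealth programme is introduced and costs are expected to fall. The section does not say which data supply A0, and it does not mention the control group.

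On the expected cost result, the abstract says "Operational costs are expected to be lower than standard care", and the Findings section repeats this. The abstract describes the intervention group as one "which follows the LIVA 2.0 in addition to the conventional preventive program".

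**The concern.** Two adjacent sections use the same cost term differently. If the analyst applies the definition of investment in Health Economic Design, the budget impact calculation counts training and preparation but leaves out the licences and coach salaries that recur every year. In a coached programme these are the running costs. A municipality deciding whether to buy the programme would see a rate of return with those costs missing.

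The second matter is the reference. A change from a person's own earlier year mixes the effect of LIVA with whatever would have happened anyway. The trial has a randomised group that shows what would have happened anyway, and the planned register linkage is not limited to one arm. Register data also do not depend on attending visits, which matters because the sample size section expects 39% and 57% drop-out at 12 months. Municipal cost-effectiveness is one of the three aims in the Background, so the result will be read.

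Third, LIVA is given on top of the conventional programme. The trial can therefore estimate what adding LIVA costs. It does not test replacing the conventional programme with LIVA.

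**Working it through.** The article states no budget impact figure, so there is none to reproduce. The check is an accounting identity plus the quantities that the article does give.

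**Notation.** R = cost in the year before baseline; T = cost with LIVA; C = concurrent cost without LIVA; I = investment cost; O = operating cost. Net return is savings minus programme cost.

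**Step 1, identity.**
- As written, with savings measured from the reference year: (R − T) − I.
- With full cost and a concurrent comparator: (C − T) − (I + O).
- As written minus full: O + (R − C).

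The O term is positive whenever there is any operating cost. The R − C term is positive only if costs would have fallen without LIVA. It is negative if they would have risen, which is what the article expects under A0. If savings are instead taken from A0, and A0 is the control arm, R − C drops out and O remains.

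**Step 2, size of O in quantities.**
- Coach time. The Intervention section says one half-time post covers 200 to 250 people, and the intervention arm has 200. So 0.5 × 200/250 = 0.4 and 0.5 × 200/200 = 0.5 of a full-time post while all are coached.
- Licences. Fees run through the intervention and retention years. If nobody leaves: 200 + 200 = 400 licence-years. Health Economic Design assumes that 20% of the initial population leaves each year. If they leave after year 1: 200 + 0.8 × 200 = 200 + 160 = 360.

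No licence fee or salary is stated, so these cannot be turned into money.

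**Step 3, direction, on an assumed index.** Take R = 100, T = 90, I = 5. The net return as written is (100 − 90) − 5 = +5. These values are illustrative and not from the article.

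| C | O | Full net return | As written minus full |
|---|---|---|---|
| 100 | 2 | +3 | +2 |
| 100 | 5 | 0 | +5 |
| 100 | 10 | −5 | +10 |
| 105 | 2 | +8 | −3 |
| 95 | 2 | −2 | +7 |

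With no time trend (C = R) the overstatement equals O. A 5% trend in either direction moves the result by 5, upward or downward.

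**Step 4, the cost expectation.** The LIVA arm bears the cost of LIVA plus whatever conventional services it uses. The control arm bears only the latter. The contrast between arms is therefore the incremental cost of adding LIVA.

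**The case against.** The strongest reply is that investment costs is loose wording for everything the municipality pays. Health Economic Design counts operational costs in the cost-effectiveness analysis, so the authors plainly know of them. This stands in part: it would be wrong to infer that operating costs are missing from the whole economic evaluation. But the term is defined in the section immediately before, and an analyst who follows that definition leaves licences and salaries out. The two sections have to be reconciled.

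The second reply is that the control arm is unmentioned rather than excluded. The Analysis Strategy applies intention-to-treat to all data and refers to between-group differences over time. The Objectives compare LIVA with the conventional programme. A0 can be read as the situation without LIVA, that is, usual municipal care. This also stands. A reader might infer that the analysis is purely before-after, but the article does not establish that. What remains is that the only references named in the section are the earlier year and A0, with no source given for A0.

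Third, a reader might infer that both faults inflate the return. The article does not support this: under its own expectation of rising costs without the intervention, comparison with the earlier year understates savings. Nor can the comparator bias be sized from the expected weight losses of 4.5 kg and 2.5 kg. That would need costs to move in proportion to kilograms, which the article does not say, and it would imply falling control costs, contrary to A0.

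Finally, cost-effectiveness is a tertiary question and the budget impact analysis supplements it. That limits the reach of the point but does not answer it.

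**Conclusion.** The point holds on the cost side. Followed as written, the budget impact calculation overstates the net return by the full operating cost. In quantities this is about 0.4 to 0.5 of a full-time coach while all 200 are coached and about 360 to 400 licence-years over two years. No monetary size can be given. The rate of return is also pushed upward if savings are positive, by an amount that depends on how the rate is defined, which the article does not state. All this rests on reading investment costs as the article itself defines them.

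On the comparator, the supported conclusion is narrower: the section does not name the randomised control arm, which leaves a time-trend bias of unknown sign. Taking both faults together, the return is overstated only if O exceeds C − R, and the article's figures cannot settle that. The unknown sign is itself a reason to use the randomised comparison.

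The expectation of operational costs below standard care does not fit an add-on design and should be reworded.

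**What to change.** In Budget Impact Analysis:

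1. Define net impact as (investment + operating costs) − savings, using the terms of Health Economic Design, and base the rate of return on the same total cost.
2. Estimate savings as the between-arm difference in register-based costs, adjusted for each person's cost in the year before baseline, with all participants analysed as randomised. The earlier year then serves as a covariate and not as the comparator.
3. Define A0 as the control arm offered the conventional programme.

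In the abstract and Findings, replace the expectation of lower operational costs with a statement about the incremental cost of adding LIVA to the conventional programme.

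The cost is rewording and a modest extra analysis of data whose linkage is already planned. On the cost side the rate of return will look less favourable. The effect of the comparator change could go either way.

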### Long-Term Follow-Up

Since the target group involves participants with chronic diseases or having a risk of chronic diseases, the effect structure of a lifestyle change will first be visible over several years. These data will not be available within the current study design, and hence, the observed effects within the given time frame will be extrapolated over time. We will develop hypotheses for the effect structure according to the literature to be able to model the long-term (5 years) effect of the intervention [41,42].

### Analysis Strategy

All data are analyzed according to the intention-to-treat principle [43]. Analyses are mainly carried out according to the two target groups. However, stratification according to participant characteristics and user experiences is applied to investigate associations between success and the different characteristics. Ordinary least square regression and difference between groups over time are used to explore significant associations. Statistical significance is inferred at a two-tailed *P* value <.05. Robust standard errors are calculated. Data are analyzed by experts in biostatistics. After the study, all data will be made accessible on request in anonymized form to allow full peer scrutiny and facilitate secondary research.

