**Objective:**

This study protocol is for a 2-year randomized controlled trial that aims to evaluate the clinical and economic effects of a primary care, anchored, collaborative, electronic health (eHealth) lifestyle coaching program (long-term Lifestyle change InterVention and eHealth Application [LIVA] 2.0) in obese participants with and without type 2 diabetes. The program’s primary outcome is weight loss. Its secondary outcome is the hemoglobin A_1c_ (HbA_1c_) level, and its tertiary outcomes are retention rate, quality of life (QOL), and cost effectiveness. Analytically, the focus is on associations of participant characteristics with outcomes and sustainability.

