### Objectives and Hypotheses

Based on our previous research, we hypothesize that eHealth lifestyle coaching with the use of LIVA 2.0 will be effective in improving diet and increasing physical activity levels, thus reducing weight and improving HbA_1c_ levels after 1 year of intervention, with a sustained effect over time. This will result in increased health and quality of life (QOL) and decreased societal costs [22-27]. We expect that municipalities will find the intervention to be a cost-effective alternative for secondary prevention targeted at citizens who are at risk of developing chronic diseases, such as severe obesity, type 2 diabetes, cardiovascular disease, and cancer, and for tertiary prevention among patients with chronic type 2 diabetes, reducing the progression of diabetes and even resulting in its complete remission. To be able to investigate effects and cost-effectiveness among obese participants and obese patients with type 2 diabetes from a municipal perspective, the two target groups of the intervention are as follows: (1) obese citizens at risk of developing chronic diseases, such as severe obesity, type 2 diabetes, cardiovascular diseases, and cancer and (2) obese patients with type 2 diabetes. The intervention is compared with the conventional preventive program that the municipality offers to these two target groups. Furthermore, we investigate associations between participant characteristics and the success of LIVA 2.0 in providing novel insights regarding the associations between participant characteristics and success with a digital lifestyle intervention from both a 1-year and over 1-year perspective.

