### Research Questions Concerning Both Target Groups

With regard to the primary outcome, the research question is as follows: What is the effect of LIVA 2.0 on users’ weight? With regard to the secondary outcome, the research question is as follows: What is the effect of LIVA 2.0 on users’ HbA_1c_ levels? With regard to the tertiary outcomes, the research questions are as follows: (1) What is the effect of LIVA 2.0 on the need for medicine use? (2) What is the effect of LIVA 2.0 on users’ QOL? (3) What is the cost-effectiveness from a municipal perspective? (4) Which participant characteristics are decisive for the effect and sustainability of LIVA 2.0?

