### Intervention

Participants in the intervention group receive login information for LIVA 2.0 at the first personal face-to-face meeting (either physical or digital), after which the health coach introduces the LIVA 2.0 app. After the first personal meeting, the same health coach will be coaching the participant throughout the period. When a health coach is on vacation or is sick for a short period, coaching is postponed. If the health coach is sick for a long period, a personal meeting with a new health coach is arranged to secure a personal relationship, after which the new health coach will be coaching the participant for the rest of the period. Based on our experiences from earlier studies, a half-time health coach can manage between 200 and 250 individuals. The participant and health coach together agree on goals for diet, physical exercise, sleep, and all other life areas of relevance to the participant. All goals are participant driven on the basis of the initial motivational interview with the health coach. The health coach is required to identify what health initiatives will benefit the participant the most based on the participant’s own wishes and to find out what is possible for the participant taking into account the participant’s personal barriers and facilitators. Using the app, the participant provides a daily record and also enters comments, concerns, and questions for the health coach, who can see the entire profile of the participant. The health coach provides individual asynchronous online consultation according to the participant’s needs and based on the participant’s registrations. The health coach encourages and praises goal attainment and endeavors to keep the participant motivated. Additionally, the health coach provides advice related to setting goals based on the SMART model (specific, measurable, attainable, relevant, and timely) [29] according to a predefined guideline structure (Table 1) [27,29].

**Table 1 table1:** Template of the Intervention Description and Replication checklist [30] for the eHealth lifestyle coaching tool (LIVA 2.0).

Item	Description

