### Conventional Care Service (Control Group)

Participants randomized to the control group are offered to receive the standard municipal secondary or tertiary preventive care service. A recent study aimed at examining Danish municipal weight loss care services and identifying and describing their content and structure found 234 different municipal weight loss care services. Although they were different, they most frequently contained information about diet and physical activity. They also sometimes included information about how to develop healthy habits, and a few of the care services even included the promotion of well-being and social participation [32]. The standard municipal care service within the control group is therefore not the same, but none of the care services resembled the LIVA 2.0 program. At follow-up measurements, the control group participants were asked to describe if they had participated in any interventions since baseline, and if so, describe the content of these interventions. This enabled a qualitative assessment and summary of the standard care services used in the control group.

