#### Explaining Variables

Each participant’s sociodemographic characteristics are obtained at the baseline face-to-face meeting and registered by the health coach. The explaining variables are used in the descriptive analyses of associations between the participants’ characteristics and the success of using LIVA 2.0.

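### The question of which characteristics decide LIVA 2.0's effect is paired with an analysis of who succeeds, and no comparison of the LIVA-versus-control difference across characteristics is stated

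*Protocol article*

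**What the plan says.** Under Research Questions Concerning Both Target Groups, tertiary question 4 reads: "Which participant characteristics are decisive for the effect and sustainability of LIVA 2.0".

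The text that bears on how it will be answered is:

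- Analysis Strategy: "stratification according to participant characteristics and user experiences is applied to investigate associations between success and the different characteristics". The next sentence names the tools: "Ordinary least square regression and difference between groups over time are used to explore significant associations". The section opens with the intention-to-treat principle and says that analyses are mainly done by the two target groups.
- Explaining Variables: the baseline variables serve descriptive analyses of the link between "characteristics and the success of using LIVA 2.0".
- Objectives and Hypotheses: "we investigate associations between participant characteristics and the success of LIVA 2.0".
- Objective, in the abstract: "the focus is on associations of participant characteristics with outcomes and sustainability".

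On who can have an experience of LIVA, the Intervention section says "Participants in the intervention group receive login information for LIVA 2.0 at the first personal face-to-face meeting". Of control care, the Conventional Care Service section says that "none of the care services resembled the LIVA 2.0 program".

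**The concern.** In a two-arm randomised trial the effect of LIVA 2.0 is the difference between LIVA and control. A characteristic is decisive for that effect only if the difference changes with it. Relating success to a characteristic answers another question: who loses weight. Some people would do better under either programme, and a trait that marks them is prognostic without telling anyone for whom LIVA adds something.

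User experiences raise a second difficulty. Read as experience of using LIVA, they develop after randomisation and only in the arm that has the app. Strata built on them have no randomised comparator, so a difference between them may reflect motivation or early progress as much as any action of LIVA.

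What is at stake is the answer to question 4, in an area that the abstract calls the analytic focus. The primary comparison of weight between the arms is not touched.

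**Working it through.** **1. What each analysis estimates.** Take a binary baseline characteristic. Let *p* be its prognostic effect on weight loss (present in both arms) and *m* the amount by which it changes LIVA's effect.

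- Contrast by characteristic within the LIVA arm: *p + m*.
- Contrast with arms pooled, 200 versus 140: *p + m* × 200/340 = *p* + 0.59*m*.
- Contrast in the LIVA arm minus contrast in control (the interaction): *m*.

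Only the third isolates what question 4 asks. The article does not state it.

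**2. How often the answers differ.** Simulation of 4,000 trials with 200 and 140 participants, no dropout, a 2 kg average LIVA effect and a balanced binary characteristic. Success is taken as kg lost. The first two contrasts use unequal-variance t tests, and the interaction uses least squares with robust standard errors, all at two-sided 0.05. The values of *p*, *m* and the SDs are assumptions. Entries are the percentage of trials with a significant result, at SD 2.5 / SD 5 kg.

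| True situation | Within LIVA arm | Arms pooled | Interaction |
|---|---|---|---|
| Prognostic only (*p* = 2, *m* = 0) | 99.9 / 81 | 100 / 95 | 5.2 / 5.6 |
| Modifier offset by prognosis (*p* = −2, *m* = 2) | 5 / 4 | 79 / 31 | 95 / 45 |
| Modifier only (*p* = 0, *m* = 2) | 100 / 80 | 98 / 56 | 95 / 44 |

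In the first row the characteristic has no influence on LIVA's effect, yet an analysis of success almost always flags it. In the second row the LIVA-arm contrast is −2 + 2 = 0, so a true modifier is missed. The pooled contrast is −2 + 2 × 200/340 = −0.82 kg, so where it is significant it points the wrong way.

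**3. What the trial can support on interactions.** Sample Size Considerations gives 55 and 32 evaluable participants per target group for a 2.0 kg difference (4.5 minus 2.5 kg), with power printed as 0.95% and read here as 95%. No SD is given, so the figure cannot be reproduced. Solving for the SD:

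SD = 2.0 / [(1.960 + 1.645) × √(1/55 + 1/32)] = 2.0 / (3.605 × 0.2223) = 2.50 kg.

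Since that SD is only implied, 4 to 6 kg is shown as an assumed range. For a balanced binary characteristic, the standard error of the interaction is SD × √(4/n_LIVA + 4/n_control), and the smallest interaction detectable with 80% power is (1.960 + 0.842) times that.

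- All 340: √(4/200 + 4/140) = 0.220, giving 1.5, 2.5, 3.1 and 3.7 kg at SD 2.5, 4, 5 and 6 kg.
- Expected completers at 12 months, 200 × 0.61 = 122 and 140 × 0.43 = 60: √(4/122 + 4/60.2) = 0.315, giving 2.2, 3.5, 4.4 and 5.3 kg.

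Power for a 1 kg interaction in all 340 is 44% at SD 2.5 kg and 15% at SD 5 kg.

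**The case against.** The best defence is that the Analysis Strategy section may already contain the right contrast. It applies intention to treat and names differences between groups over time as a tool for these very associations. In a two-arm trial, groups most naturally means the arms, and arm contrasts within strata are the first step of a subgroup analysis. This stands in part. The sentence does not say which groups are meant, though, and even on the favourable reading no comparison between strata is stated. A significant difference in one stratum and not in another does not show that the effect differs. The split by target group has the same limit: it gives an effect in each group but states no comparison of the two.

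A reader might infer that the analysis is confined to LIVA users. The Explaining Variables section leans that way, but the Analysis Strategy section contains no such restriction. A reader might also infer that every association will be screened at P<.05. The article gives one general significance level and describes no screening procedure.

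It is fair to add that the Explaining Variables section calls the analyses descriptive and that most statements speak only of associations. The word that goes further is in question 4 itself, which asks what is decisive for the effect. Descriptive labelling does not turn an association with weight loss into evidence about LIVA's effect.

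A list of characteristics and any multiplicity adjustment may properly sit in the analysis plan or in Multimedia Appendix 2, neither of which is shown. Their absence is not part of this point.

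Finally, the simulation uses chosen effects, including an exact offset, and no dropout. It illustrates the mechanism and does not forecast this trial's results. The last table row also shows that when a characteristic is purely a modifier, the LIVA-arm contrast is the more sensitive test. Its weakness is that its result cannot be told apart from prognosis.

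**Conclusion.** The concern holds as a mismatch between question and stated analysis. Question 4 asks about modification of LIVA's effect; the analysis as written can identify predictors of weight loss instead, and no section states a comparison of the arm difference across levels of a characteristic. For user experiences of LIVA, no such randomised comparison is available.

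The size depends on how strongly characteristics predict weight loss in general, which the article does not say. With an assumed 2 kg prognostic effect and SDs of 2.5 to 5 kg, false attribution occurs in 81% to 100% of trials across the within-arm and pooled analyses, against 5% to 6% with an interaction term.

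Two further inferences are not supported. One is that, because the control arm is expected to lose 2.5 of the 4.5 kg expected under LIVA, a matching share of the flagged characteristics would be spurious. That ratio compares arm means and says nothing about how any characteristic acts. The other is that municipalities would select participants on these results. The article promises new insight into the associations and describes no such use.

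**What to change.** For baseline characteristics, state that question 4 will be answered by arm-by-characteristic interactions in all randomised participants, at 12 months and, for sustainability, at 24 months. Report the LIVA-minus-control difference at each level with its confidence interval. Label these results exploratory: the trial is sized for a 2.0 kg main effect, and among expected completers only interactions of 2.2 kg or more, larger than that whole effect, could be detected with 80% power. Report associations with user experience as descriptive within the LIVA arm only, and do not word them as determinants of effect.

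The alternative is to keep the analysis and reword question 4 as predictors of weight loss among LIVA users.

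Either route changes wording and analysis only and uses variables that the trial already collects. The cost of the first is sensitivity: fewer characteristics will be declared, and a null interaction will not show that the effect is uniform. The cost of the second is that the trial no longer claims to say for whom LIVA works better than usual care.
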